## Abstract

Gait disorders are the most frequent symptoms associated to multiple sclerosis (MS). Robot-assisted gait training (RAGT) in people with MS (PwMS) has been proposed as a possible effective treatment option for severe motor disability without significant superiority when compared to intensive overground gait training (OGT). Furthermore, RAGT at high intensity may enhance fatigue and spasticity. This study aims to evaluate the effects of a low-intensity RAGT at progressively increasing intensity compared to conventional RAGT and OGT in PwMS and moderate to severe walking impairment. 24 PwMS will be recruited and assigned to one of the three treatment groups: low-intensity RAGT at progressively increasing intensity, conventional RAGT and OGT. All participants will receive 3-weekly treatment sessions of 3 hours each for 4 weeks. In the first 2 hours of treatment, all participants will receive a rehabilitation programme based on stretching exercises, muscle strengthening and educational interventions. During the last hour, subjects will undergo specific gait training according to the assignment group. Outcomes will be assessed before and after treatment and at 3-month follow-up. The primary outcome is walking speed. Secondary outcomes include mobility and balance, psychological measures, muscle oxygen consumption, electrical and haemodynamic brain activity, urinary biomarkers, usability, and acceptability of robotic devices for motor rehabilitation. The results of this study will provide a safe, affordable and non-operator-dependent, intervention for PwMS. Results in terms of functional, psychological, neurophysiological and biological outcomes will confirm our hypothesis. The study’s trial registration number: NCT06381440.

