### Sample size calculation

As this is a pilot study, the sample size does not need to be calculated.^55^ The sample planned for this preliminary study comprises 24 subjects, 8 in each intervention group.

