### Statistical analysis

Descriptive statistics (mean and 95% CI) will be reported at T0, T1 and T2 for all the variables. The distribution of data at baseline will be tested using the Shapiro-Francia tests. The baseline comparison between the three groups will be performed using the χ^2^ test for categorical variables and one-way analysis of variance (ANOVA) or the Kruskal-Wallis test for continuous variables, as appropriate. The outcome comparison between the three groups will be performed using a one-way ANOVA or Kruskal-Wallis test according to sample distribution. The intragroup comparison between T0, T1 and T2 will be performed using a t-test for paired data or a Wilcoxon test, depending on the distribution. In case of imbalances at baseline between the groups, appropriate statistical correction analyses (eg, analysis of covariance) will be adopted. Patient perspectives on the acceptability and usability of the robot intervention will be analysed using descriptive analysis for quantitative and inductive content analysis for qualitative data.^56^

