## Discussion

This pilot randomised controlled trial aimed to investigate the efficacy of robot-assisted gait rehabilitation in PwMS by identifying the robotic intervention’s loading factors, related metabolic response and the patient’s perspective. Identifying these non-operator-dependent intervention models would optimise the use of RAGT in future research studies and clinical practice.

We expect this study to observe an improvement in gait, mobility and balance in all patients, both those who received robot-assisted gait rehabilitation and those who received OGT. However, considering the results of increasing training intensity in other populations,^16 19 23^ we expect significantly greater changes in subjects assigned to the low-intensity RAGT at progressively increasing intensity group than in the other treatment groups.

Identifying the optimal dose response could be useful in PwMS, where fatigue management must be considered when defining the rehabilitation intervention and its parameters. The novelty of the intervention we will apply lies in proposing a low-intensity intervention and gradually increasing its intensity throughout the treatment sessions. This approach seems in contrast to literature recommendations regarding exercise characteristics that must be intense and high doses to promote learning mechanisms and neuroplasticity.^57 58^ The idea that more is better may not be suitable for a patient in whom symptoms like fatigue and spasticity caused by high-intensity training may compromise the effectiveness and applicability of the intervention, particularly in patients with a high disability level. Furthermore, implementing a low-intensity protocol would broaden the range of PwMS who can benefit from robotic gait therapy.

Concerning exosomal urinary miRNAs, we expect to identify one or more miRNA correlated with MS to confirm that urine is a useful body fluid for detecting molecules related to this pathology. We also expect to be able to establish one or more miRNA panels to be used as diagnostic/prognostic biomarkers of the effects of treatments, regardless of the intervention.

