Psychiatric comorbidities represent a challenge when treating patients with PwMS due to the high prevalence of these disorders and the limited evidence for the efficacy of pharmacological treatments.^59^ On the other hand, there is emerging evidence about the effectiveness of rehabilitation programmes on mood symptoms in MS patients.^60^ Consequently, we anticipate that participation in rehabilitation treatments will yield positive outcomes for all patients, irrespective of their group allocation. However, variations in the exercises’ content across the three groups, particularly in intensity, are expected to elicit distinct experiences, perceptions and emotional responses from the patients, contingent on the nature of their assigned intervention.

We assume that both quantitative and qualitative data on the usability and acceptability of the robotic intervention will provide valuable insights into the patient’s ‘lived experience’.^61^ Qualitatively exploring the unique perspectives of PwMS and severe gait disability and collecting their suggestions regarding possible barriers and strategies for participation might inform future intervention implementation.^62^ Since RAGT is safe and well tolerated by patients with MS,^63^ we expect patients to provide positive feedback on the robotic intervention.

Our study may have some limitations. First, the pilot nature of the study does not allow any definitive conclusions due to the low number of subjects recruited. Second, the absence of a follow-up evaluation of more than 3 months does not allow us to conclude the effectiveness of the low-intensity intervention at progressively increasing intensity over time.

If the pilot study’s findings confirm our hypothesis, a randomised trial on a larger group of subjects would allow us to confirm our results.

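### The planned omnibus test and within-arm tests do not answer the expectation that low-intensity progressive RAGT beats each of the two comparators

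*Protocol article*

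**What the plan says.** The expectation is directional and names two comparators. In the Discussion the investigators write that "we expect significantly greater changes in subjects assigned to the low-intensity RAGT at progressively increasing intensity group than in the other treatment groups". The abstract also gives the aim as comparing low-intensity progressive RAGT with conventional RAGT and with overground training (OGT).

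The Statistical analysis section fixes three things:

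- Between arms: "The outcome comparison between the three groups will be performed using a one-way ANOVA or Kruskal-Wallis test according to sample distribution".
- Adjustment, conditional on what is observed: "In case of imbalances at baseline between the groups, appropriate statistical correction analyses (eg, analysis of covariance) will be adopted".
- Within arms: "The intragroup comparison between T0, T1 and T2 will be performed using a t-test for paired data or a Wilcoxon test".

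It names no contrast of low-intensity RAGT with either comparator. Means with 95% CIs are promised as descriptive statistics at each time point, not for a difference between arms.

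On size: "The sample planned for this preliminary study comprises 24 subjects, 8 in each intervention group", with no calculation.

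On interpretation, the abstract says: "Results in terms of functional, psychological, neurophysiological and biological outcomes will confirm our hypothesis". The Discussion concedes that so small a pilot permits no definitive conclusion, and closes by saying that, if the pilot's "findings confirm our hypothesis, a randomised trial on a larger group of subjects would allow us to confirm our results".

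**The concern.** The expectation amounts to two comparisons: low-intensity against conventional RAGT, and low-intensity RAGT against OGT. An omnibus test asks whether any of three means differ, in any direction. A significant result fits low-intensity RAGT being best, being worst, or equalling conventional RAGT while OGT lags.

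The only other inference in the plan is within arms. All arms receive the same first 2 hours of rehabilitation in every 3-hour session, and the Discussion expects gait, mobility and balance to improve in all patients. A significant gain from T0 in one arm therefore cannot be credited to that arm's gait training. A significant gain in one arm beside a non-significant gain in another is not evidence that the arms differ.

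At stake is whether the report answers the question that the trial was set up to ask. There is also a risk that a pilot of 24 is reported as confirming a hypothesis its analysis did not address.

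**Working it through.** **Inputs from the article.** 3 arms; 8 patients per arm; assessments at T0, T1 and T2; primary outcome T25-FW. The article gives no alpha, SD, effect size or power, so it contains no figure to reproduce.

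**Assumptions.** Two-sided 5% level; SD 1 for the between-arm outcome; normal data; no dropout.

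**1. Can the omnibus test identify the better arm?**
F test with 2 and 21 df, critical value 3.467. Noncentrality λ = n × Σ(μᵢ − μ̄)², with means in the order low-intensity, conventional, OGT.

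| True means (SD units) | λ | P(significant) | Expectation true? |
|---|---|---|---|
| 1, 0, 0 | 8 × 0.667 = 5.33 | 47% | yes |
| 1, 1, 0 | 8 × 0.667 = 5.33 | 47% | no: equals conventional RAGT |
| 0, 1, 1 | 8 × 0.667 = 5.33 | 47% | no: worst arm |

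The three situations have the same λ, so the test cannot tell them apart.

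**2. Can within-arm tests fill the gap?**
Suppose all arms truly gain by the same amount g, in SDs of the change score. The paired t-test with n = 8 (7 df, critical value 2.365) has noncentrality g√8 and power p. The arms are independent, so the probability that low-intensity RAGT is significant while at least one comparator is not is p(1 − p²).

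| g | p | p(1 − p²) |
|---|---|---|
| 0.3 | 0.114 | 11% |
| 0.5 | 0.232 | 22% |
| 0.8 | 0.496 | 37% |
| 0.9 | 0.591 | 38% |
| 1.0 | 0.681 | 37% |
| 1.2 | 0.828 | 26% |
| 1.5 | 0.951 | 9% |

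The maximum of p(1 − p²) is 38.5%, at p = 0.577. Over the assumed gains the range is about 9% to 38%.

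**3. False positives among the within-arm tests, with no change in any arm.**
- T0 to T1 only: 3 independent tests, 1 − 0.95³ = 14%.
- All pairs of time points: 3 arms × 3 pairs = 9 tests per outcome. Tests within an arm are correlated, so this was simulated: 34%, and almost the same for correlations between time points from 0.3 to 0.95. If all nine were independent, it would be 1 − 0.95⁹ = 37%.

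**4. What precision would a direct contrast have?**
Half-width of the 95% CI for one pairwise difference = t × √(2/8) = 0.5t. With the pooled three-arm variance (21 df) this is 0.5 × 2.080 = 1.04 SD. With two arms only (14 df) it is 0.5 × 2.145 = 1.07 SD. Adjustment for T0 would narrow it by an amount that depends on the baseline correlation, which the article does not give.

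**The case against.** **Pairwise comparisons may sit in a document not shown.** An article need not list follow-up tests, and their absence alone would be no finding. But the article does fix a between-arm method, makes baseline adjustment depend on observed imbalance, and commits to significance tests within arms. Those choices can be judged as written.

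**The expectation stands in the Discussion, while the declared primary aim concerns load factors and variability of response.** This is true. Still, the abstract sets out the three-arm comparison as the study's aim, and the randomised design serves that comparison.

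**A pilot needs no power calculation.** The article says so: "As this is a pilot study, the sample size does not need to be calculated". This is accepted, and the point does not ask for a larger sample.

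Three stronger readings are tempting and are not supported:

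- A reader might take the Discussion's closing sentence as a go/no-go rule based on significance. It is a remark about what a larger trial could do. It names no p-value and no threshold, does not say that a larger trial follows only on confirmation, and stands beside an admission that the pilot cannot be definitive. A rate of wrongly abandoned treatments would measure a rule that the article does not contain.
- A reader might infer that within-arm p-values will drive the conclusions. The article assigns the comparison of arms to the omnibus test. The within-arm tests can mislead, but nothing says that arms will be ranked by them.
- A reader might use the 20% figure in the Introduction as a criterion for going on. There it is a minimal clinically important difference in walking speed, used in a cited study to classify responders. It is not a margin between arms, and T25-FW is recorded as time.

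**Conclusion.** The point holds in this limited form. The between-arm analysis does not match the stated expectation: the omnibus test is significant 47% of the time in two situations where the expectation is false, exactly as often as where it is true by 1 SD. The within-arm tests do not repair this. They produce a misleading pattern in favour of low-intensity RAGT in about 9% to 38% of trials with equal true gains, and at least one false positive per outcome in 14% (T0 to T1 only) to 34% (all nine tests) of trials with no change.

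These sizes rest on an assumed 5% two-sided level, assumed effect sizes, normal data and 8 evaluable patients per arm. The mismatch itself rests on none of them. The abstract's assertion of confirmation also conflicts with the Discussion's own statement of limits. The change should be made; the trial's design and sample size are not called into question.

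**What to change.** 1. For T25-FW at T1, prespecify two contrasts: low-intensity minus conventional RAGT, and low-intensity RAGT minus OGT. Take both from one model that always adjusts for the T0 value, whether or not imbalance is seen. Report each with a 95% CI, and apply Holm's adjustment if p-values are shown. Keep the planned multiple imputation.
2. Show within-arm changes from T0 to T1 and T2 descriptively, without p-values.
3. Reword the abstract's sentence on confirmation so that it agrees with the Discussion's statement that the pilot cannot be definitive. Describe the case for a larger trial through the estimates and their precision.

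No new patients, visits or measurements are needed. The cost is slightly more analysis work and a documented change to the plan. The report will also carry intervals with a half-width of about 1 SD before adjustment, in place of a significance claim.

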### Selection criteria and recruitment of participants

PwMS will be included if they meet the following inclusion criteria: (a) men and women between 18 and 65 years; (b) diagnosis of MS (primary or secondary progressive) without relapses in the preceding 3 months; (c) disability rate defined by Expanded Disability Status Scale score from 6 to 7^29^; (d) ability to perform the Timed 25-Foot Walk (T25-FW) test^30^ and (e) Mini-Mental Status Examination score ≥24/30.^31^

PwMS will be excluded if they have (a) other (neurological) conditions that may affect motor function; (b) medical conditions might interfere with the ability to complete the study protocol safely; (c) the presence of spasticity with a modified Ashworth Scale (MAS) score >3 or retractions limiting the range of motion of the hip, knee or ankle; (d) MS relapses or medication changes, or any other confounding factors during the study period and (e) rehabilitation treatment or botulinum toxin injection in the 3 months preceding the start of the study.

During the first appointment, potential participants will be informed about all the study procedures and screened following the inclusion criteria. If the inclusion criteria are met, potential participants will be given a study information leaflet detailing the study’s objectives, procedures, time frame, risks and potential benefits, as well as the telephone contact details of the staff involved and the Consent Form. A copy of the Consent Form is available as online supplemental material. In the following 3 days, candidates will be contacted by telephone and asked about their decision. For those who decide to participate, an appointment will be scheduled at which signed informed consent will be requested, and a physiotherapist will perform baseline assessments. The total number of subjects screened will be recorded according to the Consolidated Standards of Reporting Trials guidelines (figure 1).

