### Outcome assessment and data collection

The same physiotherapist will record all outcome measures at the Operative Unit of Physical and Rehabilitation Medicine of Ferrara University Hospital, blinded to the randomisation list. Clinical and instrumental evaluation will be performed before (T0) and after (T1) the twelve sessions of treatment and at 3-month follow-up (T2).

A clinical psychologist with expertise in MS from the Department of Neuroscience, Biomedicine and Movement Sciences at the University of Verona will remotely assess the robot technology’s usability, acceptability and perceived pleasantness. The assessor will be blinded to the patient allocation group, and the evaluation will be performed only at T1.

A team member will record each participant’s general demographic information, including age and gender, as well as their comorbidities and medical history (table 1).

**Table 1 T1:** Schedule of enrolment, interventions and assessment

Time point	Study period				
	Enrolment	Allocation	Postallocation		Close-out
	T-1		T0	T1	T2
Enrolment					
Eligibility screen	X				
Informed consent	X				
Allocation		X			
Interventions					
Low-intensity RAGT at progressively increasing intensity					
Conventional RAGT assessments					
OGT					
Primary outcome					
T25-FW			X	X	X
Secondary outcome					
Clinical measures and questionnaires			X	X	X
Psychological assessment			X	X	X
Haemodynamic and metabolic evaluations			X	X	X
Electrical brain activity			X	X	X
Laboratory-based measures			X	X	
Acceptability of robot intervention				X	

OGT, overground training; RAGT, robot-assisted gait training; T0, before treatment; T-1, enrolment time; T1, post-treatment; T2, 3 months follow-up; T25-FW, Timed 25-Foot Walk test.

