### Primary outcome: walking function

The T25-FW test will be the primary outcome as a relevant indicator of current and future disability,^30^ a component of the MS functional composite.^32^ The patient will be instructed to walk 25 ft as fast as possible but safely, and the time will be recorded.

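### Adjusting for baseline only when the arms look imbalanced makes the T25-FW comparison less precise than it could be and leaves the model open until the data are seen

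*Protocol article*

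**What the plan says.** All of the following is in the Methods of the protocol article.

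- **Primary outcome: walking function.** "The T25-FW test will be the primary outcome as a relevant indicator of current and future disability". Table 1 schedules it at T0, T1 and T2.
- **Sample size calculation.** "As this is a pilot study, the sample size does not need to be calculated", and "The sample planned for this preliminary study comprises 24 subjects, 8 in each intervention group".
- **Statistical analysis, between-arm test.** "The outcome comparison between the three groups will be performed using a one-way ANOVA or Kruskal-Wallis test according to sample distribution". The section does not say whether T1 values or changes from T0 are compared.
- **Statistical analysis, baseline.** The arms are tested against each other at baseline (chi-square, ANOVA or Kruskal-Wallis). Then: "In case of imbalances at baseline between the groups, appropriate statistical correction analyses (eg, analysis of covariance) will be adopted". ANCOVA is only an example, and neither the covariate nor the meaning of imbalance is given.
- **Statistical analysis, distribution.** "The distribution of data at baseline will be tested using the Shapiro-Francia tests". No other distribution test is named.

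**The concern.** The default comparison ignores the baseline value of the primary outcome, although it is collected. Adjustment enters only after someone has looked at the baseline data and judged the arms unequal.

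Two things are wrong with that order:

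- **The purpose of adjustment.** Covariate adjustment in a randomised trial mainly removes outcome variance that the baseline explains. That gain is there whether or not the arms happen to differ at T0, so an observed imbalance is the wrong condition for using it.
- **The freedom it leaves.** With no threshold and no named covariate, the analyst decides after seeing the data which model answers the primary question.

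This is a rule the article states, not a detail it leaves out. An analysis plan that followed it would carry the same weakness.

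With 8 patients per arm, precision is scarce. The Discussion predicts a significantly larger improvement in the low-intensity progressive arm and ties a larger trial to these findings, so the between-arm estimate will be read.

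**Working it through.** **Inputs from the protocol.** Three arms, n = 8 each; T25-FW at T0 and T1. The plan has no power figure to reproduce.

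**Assumptions, none given in the protocol.** Two-sided 5% level; normal data with SD 1 at T0 and T1; one arm better by d = 0.8 SD; baseline-to-T1 correlation ρ of 0.5, 0.7, 0.8 or 0.9; imbalance means a baseline test with p < 0.05.

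**Step 1: residual variance.** T1 values: 1. Change scores: 2(1 − ρ). ANCOVA: 1 − ρ², times about 1.05 for estimating the slope. The standard error of a difference between two arms is √(2/8) = 0.5 times the square root of that variance:

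| ρ | T1 values | Change | ANCOVA |
|---|---|---|---|
| 0.5 | 0.50 | 0.50 | 0.44 |
| 0.7 | 0.50 | 0.39 | 0.37 |
| 0.8 | 0.50 | 0.32 | 0.31 |
| 0.9 | 0.50 | 0.22 | 0.22 |

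**Step 2: power by noncentral F.** With one of three arms shifted, λ = n·d²·(2/3) / residual variance. On T1 values λ = 8 × 0.64 × 2/3 = 3.41, and with 2 and 21 df the power is 31.8%. At ρ = 0.8:

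- Change scores: λ = 3.41/0.40 = 8.53, power 68%.
- ANCOVA: λ = 3.41/(0.36 × 1.05) = 9.03 with 2 and 20 df, power 70%.

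**Step 3: the trigger (simulation).** A 5% test fires in about 5% of randomised trials, because any baseline difference there is chance. The two most distant arms differ by at least 0.5 SD in about 58% of trials, and about 91% of those are not flagged. On T1 values at ρ = 0.8, an unflagged 0.5 SD gap moves the contrast by 0.5 × 0.8 = 0.4 SD.

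**Step 4: power of the whole rule (simulation; repeat runs agree to about one point).**

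| ρ | Rule, T1 values | Rule, change | ANCOVA always | Relative loss, T1 | Relative loss, change |
|---|---|---|---|---|---|
| 0.5 | 32% | 32% | 40% | 1 − 32/40 = 20% | 20% |
| 0.7 | 31% | 49% | 54% | 1 − 31/54 = 43% | 9% |
| 0.8 | 32% | 68% | 70% | 1 − 32/70 = 54% | 3% |
| 0.9 | 33% | 94% | 94% | 1 − 33/94 = 65% | 0% |

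On T1 values the rule performs almost exactly like the unadjusted test, because it adjusts so rarely.

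**Step 5: a trigger based on size.** If imbalance means an observed gap of at least 0.5 SD, power on T1 values is about 35% at ρ = 0.5 and 41% / 49% / 62% at 0.7 / 0.8 / 0.9. The relative loss at those three values is 1 − 41/54 = 24%, 1 − 49/70 = 30% and 1 − 62/94 = 34%.

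**Step 6: type I error of the rule on T1 values, 5% trigger.** About 4.4% / 3.8% / 3.4% / 2.4% at ρ = 0.5 / 0.7 / 0.8 / 0.9.

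**Step 7: choice of ANOVA or Kruskal-Wallis.** On normal T1 values at d = 0.8, power is 32% against 29%. On lognormal data (sigma 0.6) the two are equal at about 29%. The choice between these tests contributes little to the loss.

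**The case against.** The strongest reply is that this is a pilot without a power calculation that disclaims definitive conclusions, so no planned power is lost. The protocol also does not say that imbalance means a significant test, and the Discussion words its expectation in terms of change, where little is lost at high correlation. All of that stands. It limits the size and severity of the point but does not justify making adjustment conditional: even on change scores ANCOVA is never materially worse here, and the trigger remains undefined.

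A reader might infer several stronger points that the documents do not support:

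- **More than half the power is lost.** At d = 0.8 that needs T1 values, a 5% test as trigger and a correlation of about 0.8 or more. The protocol states none of these.
- **False positives are inflated.** Overall type I error under the rule is below 5%.
- **A baseline normality test picks the outcome test.** It is the only distribution test named, so the inference is reasonable, but the text says only that the choice follows the sample distribution. The effect is small in any case.
- **The chi-square test undermines the trigger.** With 8 per arm, expected counts for a binary variable are small, but T25-FW is continuous and would not pass through that test.
- **The baseline is contaminated by knowledge of the arm.** Table 1 places T0 under "Postallocation", while the recruitment section says that at the consent appointment "a physiotherapist will perform baseline assessments". The table's note defines T0 as before treatment, and nothing says that patients know their arm then. At most the order could be clarified.

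**Conclusion.** The concern holds in a limited form. Making adjustment for baseline T25-FW depend on an undefined imbalance is a poor rule, and it leaves the primary model to be settled after the data are seen.

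Its cost depends on unstated quantities. For d = 0.8 SD, correlations of 0.5 to 0.9 and a 5% trigger, it is about a fifth to two thirds of the power if T1 values are compared, and about 20% down to nothing if changes are compared. For a pilot the better expression is precision: at a correlation of 0.8, the standard error of a pairwise difference is 0.50 SD unadjusted against about 0.31 SD with ANCOVA.

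The error rate is conservative, so this is not a validity failure. The point should be fixed but ranks below a must-fix.

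**What to change.** Replace the conditional rule with one prespecified primary analysis: ANCOVA of T25-FW at T1 on arm, with T25-FW at T0 always included, whatever the baseline looks like. Fix the scale for outcome and covariate in advance, for example log time. Log speed then gives the same comparison with the sign reversed, which also settles the difference between the abstract (walking speed) and the outcome section (time).

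Use the same model at T2 as secondary and a rank-based ANCOVA as the sensitivity analysis. Keep the baseline table as description, and do not let baseline significance tests or a baseline normality test choose the model.

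The statistical cost is one degree of freedom (21 error df become 20). No new data are needed. Since enrolment began in November 2023, date the change and make it before outcome data and group assignments, which the protocol keeps in separate datasets, are joined.
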